### Statistical analysis

Patients’ characteristics will be analysed descriptively. Measures of mobility (LEPF and life-space) will be analysed (descriptive statistics and 95% confidence intervals) for the total sample and stratified by predefined subgroups (based on demographic characteristics and stroke severity). Linear mixed effects models will be used to model the trajectories of mobility measures for the total sample and for predefined subgroups [104, 105]. Time will be modelled as a discrete variable indicating the time points (T_0_, T_1_, T_2_, T_3_). Comparison of trajectories between subgroups will be assessed using likelihood ratio tests [106]. Tukey post-hoc tests will be applied to compare subgroups at specific time points. Diagnostic residual plots will be applied to assess the model fit. Measures of mobility will be transformed (e.g., log) in the case of inadequate model fits.

As an exploratory analysis, growth mixture models (GMMs) will be used to identify relevant subgroups with different trajectories [104, 107–109]. GMMs identify multiple latent classes that have similar trajectories over time. The number of latent classes to be extracted must be set in advance. We will fit GMMs with two to five classes. The model selection will be done based on the lowest value of the Akaike Information Criterion (AIC) and lowest value of the Bayesian Information Criterion (BIC) [108]. After identifying relevant subgroups with different trajectories using GMMs, multinomial logistic regression models will be used to identify predictors of group-membership [110].

As a secondary analysis, we will use linear mixed effect models to test whether changes in LEPF parameters are associated with changes in life-space [111]. Specifically, the changes in life-space between each time point serves as the dependent variable and the changes in LEPF parameters serve as predictors.

Data from the map-based tool including reasons for going outdoors, transportation use, distances covered and assistance needed will be analysed descriptively (frequencies and proportions with 95% confidence intervals) by subgroups of age, sex, stroke severity, housing/living situation, and residential area.

We set the significance level at 5% and will use two-sided tests throughout our analyses.

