### Sample size calculation

We used simulations to estimate the required sample size for a linear mixed effects model assessing the trajectory of 10 m habitual walking speed over 4 time points [112]. Specifically, we powered the analysis to detect an overall trend over time as well as clinically significant differences of 0.14 m/s between each adjacent time point [13, 113, 114]. Based on prior studies, the standard deviation of the walking speed was assumed to be 0.3 m/s at each time point [13, 66, 113–116]. We found no information in the literature about the correlation of walking speed within each subject between time points. Accordingly, we performed multiple simulations for correlations between time points of 0.2, 0.5, 0.6, and 0.7, while keeping all other parameters fixed. For each assumed correlation, a simulation with 5000 repetitions to assure robust estimation was performed to estimate the required sample size. All hypothesis tests were two-sided with a significance level of 5% while the statistical power was set at 80%. We inflated the required sample sizes to adjust for an anticipated dropout rate of 5% between each time point.

Assuming a correlation of 0.2 of walking speed between time points, 117 subjects were needed to achieve the required power of 80%. The corresponding sample sizes were 74, 59 and 45 for correlations of 0.5, 0.6 and 0.7, respectively (Fig. 2). We think that a correlation of at least 0.6 is plausible for these data. Thus, we decided to at least recruit 59 subjects.

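### In the trajectory comparisons, test stroke severity (and age, if it is used) as a continuous covariate-by-time term, and keep the predefined subgroups for display

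*Protocol article*

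**What the plan says.** The Statistical analysis section first describes the mobility measures for the whole sample and "stratified by predefined subgroups (based on demographic characteristics and stroke severity". It then fits linear mixed models to the whole sample and to those predefined subgroups, with time as four discrete points. The formal step follows: "Comparison of trajectories between subgroups will be assessed using likelihood ratio tests", with Tukey post-hoc tests at specific time points. The error rate is general: "We set the significance level at 5% and will use two-sided tests throughout our analyses". No continuous age or severity term is described in these models.

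The Participant characteristics section shows that age is recorded at first admission. NIHSS is recorded on admission, at 24 hours, at T0 and at T3.

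Two other analyses in the same section are relevant. An exploratory growth mixture analysis is followed by multinomial regression on class membership, with no statement that its predictors are categorised. The map-tool data are reported "by subgroups of age, sex, stroke severity, housing/living situation, and residential area", but only as frequencies and proportions with confidence intervals.

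**The concern.** The likelihood ratio comparison is a test, not a stratified description, and it treats a score as a set of groups. Under a smooth relation, patients on either side of a cut are treated as different, and patients far apart on the same side as alike. The comparison then has less power than the same data allow, and its result depends partly on where the predefined cut lies.

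This matters because the study is small and was sized for something else. The Sample size calculation section says "we powered the analysis to detect an overall trend over time as well as clinically significant differences of 0.14" m/s between adjacent visits, which is change over time in the whole sample. No power was set aside for comparing trajectories between kinds of patient, yet that comparison is the non-exploratory test that bears on which patients recover differently.

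**Working it through.** **Inputs from the article.** Two-sided 5%; N = 59; 5% dropout per interval, so 59 × 0.95³ = 50.6, or about 50 completers; a likelihood ratio test over four discrete time points.

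**Assumed, because the article gives no figure.** A linear covariate effect; a median split unless stated; a correlation r of 0.2 to 0.5 between covariate and change in the mobility measure.

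**1. The plan's own figure.** The only power statement is N = 59, under the rule "All hypothesis tests were two-sided with a significance level of 5% while the statistical power was set at 80"%. With SD 0.3, correlation 0.6 and steps of 0.14 m/s, simulation gives these numbers of subjects (after dropout inflation in brackets):
- one unadjusted adjacent contrast: 30–31 (35–37)
- all three unadjusted: 45 (53)
- all three with Bonferroni: 57 (67)

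A Scheffé threshold for one contrast gives 116, 74, 60 and 45 after inflation, against the stated 117, 74, 59 and 45, but the article does not mention that method. The success criterion of the simulation is not stated, so failing to match 59 does not show that it is wrong. About 50 completers give about 87% power for all three unadjusted contrasts. Nothing below depends on this figure.

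**2. Information kept.** A normal covariate and its median split correlate √(2/π) = 0.798, and 0.798² = 0.637. Since 59 × 0.637 = 37.6, the split is like losing about 21 of 59 people. Thirds keep 0.793 but use more degrees of freedom.

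**3. Starting from 80% power.**
- 1 df: (1.960 + 0.842) × 0.798 = 2.235; Φ(2.235 − 1.960) = 60.8%.
- 3 df (covariate by four time points): noncentrality 10.90 × 0.637 = 6.94, giving 58.6%.
- Simulation at N = 59: 79.9% falls to 59.6%.
- Thirds: 60.1% (2 df) or 56.9% (6 df).

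**4. By size of effect.** Power = Φ(√(N − 3) × atanh(r) − 1.960), with 0.798r in place of r for the split. At N = 59 and r = 0.35, the continuous term gives 7.483 × 0.3654 = 2.735, so Φ(0.775) = 78.1%. The split gives 7.483 × 0.2869 = 2.147, so Φ(0.187) = 57.4%.

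| r | Continuous | Median split | Loss (points) |
|---|---|---|---|
| 0.20 | 32.9% | 22.5% | 10 |
| 0.25 | 48.1% | 32.7% | 15 |
| 0.30 | 63.9% | 44.7% | 19 |
| 0.35 | 78.1% | 57.4% | 21 |
| 0.40 | 88.7% | 69.7% | 19 |
| 0.50 | 98.4% | 88.5% | 10 |

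At N = 50 the losses at r = 0.20, 0.40 and 0.50 are 9, 21 and 14 points.

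**5. Other covariate shapes.** These are simulations at N = 59 with the continuous test at 80% and a median split:
- uniform: 66.4% (loss 14)
- NIHSS-like skewed count: 55.0% (loss 25)
- lognormal: 45.0% (loss 35)

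The skewed cases assume a linear effect on the raw score. If the effect of a lognormal score is linear in its logarithm, the median split gives the same two groups and the loss returns to the normal case.

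**6. Threshold effect.** If the true effect is a step exactly at the cut, the split is the right model and loses nothing. The factor 0.798 then counts against the linear term.

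**7. Margin available.** The article states that "the standard deviation of the walking speed was assumed to be 0.3" m/s and "We think that a correlation of at least 0.6 is plausible for these data". The SD of a change is then √(2 × 0.09 × 0.4) = 0.268. For a 0.14 m/s difference in change between two equal halves of 59, 0.14/0.268 × √(29.5/2) = 2.00, so power is Φ(0.04) = 51.7%, or 45.4% with 25 per half. The article does not name 0.14 as a subgroup difference, so this is only an illustration that there is little to spare.

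**The case against.** The strongest reply has five parts.

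- **The plan is not confined to subgroups.** The mixture-model route ends in a multinomial regression that can take age and NIHSS as continuous, and it matches the wording of objective 2 at least as closely as the predefined-subgroup comparison. This stands against any reading that the plan uses these variables only as categories. It does not remove the point: that route is exploratory, rests on classes estimated from 59 people, and predicts class membership rather than testing differences in trajectory.
- **Age is not named for the trajectory models.** The text there refers to demographic variables in general. Age is named as a subgroup variable only for the map-tool data, which are descriptive and give no support to a claim about power. This stands. The point therefore rests on severity, which is named, and extends to age only if age is used.
- **No loss of power can be read from the article.** It states no effect, cut or number of groups. This stands, and the loss can only be given as a range.
- **Linearity is doubtful for NIHSS.** Only ambulatory patients with mRS up to 3 enter, so the score may be skewed and its range narrow. This limits how firmly a linear form can be assumed, and it is why the form should be fixed in advance.
- **Predefined clinical groups are legitimate and easy to interpret, and covariate coding often belongs in the SAP.** This is true, and the absent cut-points are not held against the article. But the article does fix the test as one between subgroups, and that choice can be improved.

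**Conclusion.** The point holds as a modest gain in efficiency. It does not identify an error. In the mixed-model trajectory comparisons, severity (and age, if used) is tested only between categories although numeric values are collected. Under a roughly linear effect, a comparison that would have 80% power has about 60% after a median split of a normal covariate. The loss is about 10 to 21 points across correlations of 0.2 to 0.5 at N = 59, and about 14 to 35 points for the other shapes tried at 80% reference power. It is little or none if the effect is a true threshold near the cut.

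A reader might infer three stronger things that the document does not support:
- That the study loses about 20 points of power outright. That figure needs an assumed effect, cut and shape, and the correlations near 0.35 that produce it are where the loss is close to its largest.
- That objective 2 is served only by categorised covariates. The multinomial model may use continuous ones.
- That 59 is too few. The sample size answers a different question, and this check does not show it to be wrong.

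**What to change.** In the analysis plan, make the likelihood ratio test of continuous NIHSS-by-time the main comparison of trajectories by severity, and do the same for age-by-time if age is one of the demographic variables. Name the single NIHSS measurement to be used. Prespecify its functional form, for example log(NIHSS + 1), on the grounds of the expected shape of the relation and not because the score turns out skewed. State how linearity will be checked; the residual plots already planned can serve. Sex and other truly categorical variables stay as groups. Keep the predefined categories for tables, plots and Tukey comparisons.

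This needs no new data, visits or participants, only a few sentences of wording. The downside is small: a functional form has to be assumed, and with 59 people it can be checked only roughly.

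### The only pairwise follow-up named for subgroup trajectories compares levels at single visits, so it cannot show which subgroups differ in recovery, or when

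*Protocol article*

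**What the plan says.** The Statistical analysis section of the protocol article describes mobility measures for the whole sample and "stratified by predefined subgroups (based on demographic characteristics and stroke severity"). Trajectories are fitted by linear mixed effects models, in which "Time will be modelled as a discrete variable indicating the time points" T0 to T3 (3, 6, 9 and 12 months after stroke). Two inferential steps are then named for the subgroups:

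- Overall test: "Comparison of trajectories between subgroups will be assessed using likelihood ratio tests".
- Follow-up: "Tukey post-hoc tests will be applied to compare subgroups at specific time points".

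No between-subgroup contrast of change is named, either from T0 or between visits. The section does not say whether the likelihood ratio test removes the subgroup-by-time interaction alone or the subgroup main effect as well. Nor does it make the Tukey tests conditional on a significant overall test.

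The first item under Objectives covers both mobility and its change over the first year. The Sample size calculation treats change between visits as the quantity of interest, since it is powered for "clinically significant differences of 0.14 m/s between each adjacent time point".

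**The concern.** A Tukey comparison at one visit has the null hypothesis that the subgroups have the same mean at that visit. Two trajectories have the same shape when the gap between them is constant, whether or not that gap is zero. The two hypotheses coincide only if the subgroups start level. In a randomised trial they do so in expectation. Here the subgroups are formed by severity and demographics and are first measured three months after stroke, so a gap at T0 is plausible.

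This has two consequences. If recovery is parallel, the tests at T1, T2 and T3 detect the T0 gap again and say nothing about recovery. If one subgroup catches up, the level test at T3 has nothing left to find, although the change since T0 differs most at that visit. In neither case does the follow-up show between which subgroups, or in which interval, recovery differed. The article's Background gives timing of recovery as a main reason for the study, so this is the information a follow-up to the trajectory test should supply.

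**Working it through.** **Inputs from the Sample size calculation.** "the standard deviation of the walking speed was assumed to be 0.3 m/s at each time point"; correlation 0.6 ("We think that a correlation of at least 0.6 is plausible for these data"); N = 59; two-sided 5%.

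**Assumed, because the article gives no figures.** Two subgroups of 29 and 30; gaps of 0.14, 0.20 and 0.28 m/s; equal correlation between all visits; no dropout; known variance. With two subgroups, Tukey's test at a visit is an ordinary two-group test.

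**1. The plan's own figure.** The article does not state its power rule. One inferred rule reproduces it: 80% joint power for all three adjacent differences of 0.14 m/s, each tested at 0.05/3, then a single 5% inflation. At correlation 0.6 this needs 56 evaluable subjects, and 56/0.95 = 58.9, so 59. The same rule gives 117, 74 and 45 at correlations 0.2, 0.5 and 0.7, as stated. The inputs are therefore read correctly, and the sample size is not in dispute here.

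**2. Standard errors.** √(1/29 + 1/30) = 0.2604.
- Level gap at one visit: 0.3 × 0.2604 = 0.0781 m/s.
- SD of a within-person change: 0.3 × √(2 × (1 − 0.6)) = 0.2683 m/s.
- Between-subgroup difference in change: 0.2683 × 0.2604 = 0.0699 m/s.

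**3. Constant gap, identical recovery.** Probability that a visit is flagged ≈ Φ(gap/0.0781 − 1.96).

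| Gap (m/s) | z | Flagged at a given visit | Change contrast T0 to T3 | Interaction test (3 df) |
|---|---|---|---|---|
| 0.14 | 1.79 | about 43% | about 5% | about 5% |
| 0.20 | 2.56 | about 72–73% | about 5% | about 5% |
| 0.28 | 3.58 | about 95% | about 5% | about 5% |

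Simulation with 20,000 repetitions agrees: 43–44%, 72–73% and 95% per visit.

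**4. Full catch-up, gap falling linearly from 0.28 to 0.**
- Level tests at T0, T1, T2, T3 (simulated): 95%, 67%, 22%, 5%.
- Change contrast T0 to T3: 0.28/0.0699 = 4.01, so Φ(4.01 − 1.96) = about 98%.
- Interaction likelihood ratio test: the gaps are 0.280, 0.187, 0.093 and 0, with squared deviations from their mean summing to 0.0436. Divided by 0.09 × 0.4 × (1/29 + 1/30) = 0.00244, this gives a noncentrality of 17.8 on 3 df and power of about 96%.

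**5. Smaller catch-up, 0.14 to 0.** Level tests 44%, 22%, 9%, 5%; change contrast 52%; interaction test 40%.

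**6. Overtaking, +0.14 to −0.14.** Level tests 43%, 9%, 9%, 44%; change contrast 98%; interaction test 96%.

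**7. If the likelihood ratio test drops subgroup and interaction together (4 df).** A constant 0.28 m/s gap is then itself declared a trajectory difference in about 95% of runs.

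**8. With dropout.** A separate simulation (2,000 trials, 30/29, 5% loss per interval) gives the same picture. For a constant 0.20 m/s gap the T3 level test rejects in 65% and contrasts of change stay at 4–6%. For catch-up from 0.28 the T3 level test rejects in 6% and the change contrast has 95% power.

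**The case against.** The strongest reply is that the plan gives the trajectory question to the likelihood ratio test and the level question to the Tukey tests, and that each test suits its own question. Much of this stands. With a constant gap the subgroups do differ in level at every visit, so the 43%, 72% and 95% are power for a true difference, not false positives. With full catch-up the subgroups are equal at T3, and a null result there is correct. Level is also a legitimate target under the first objective. If the Tukey tests ran only after a significant interaction test, a purely constant gap would reach them in only about 5% of runs.

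Two stronger readings are tempting, and the documents support neither. A reader might infer that the level tests flag any T0 gap. That depends on its size: 0.14 m/s is flagged at a given visit in only about 43% of runs. A reader might also infer that the plan misses subgroups that catch up. That is true of the T3 test alone. In the 0.28 m/s case the T0 test flags the gap in 95% of runs, the sequence of significant at T0 and non-significant at T3 appears in 91%, and an interaction test detects the catch-up in about 96%. That sequence is not a test of change, however: it also arises in 15% of runs with a constant 0.14 m/s gap.

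It can also be said that a condensed article need not list every contrast. But the article does choose its follow-up test, and the one it chooses cannot locate a difference in recovery. Neither the terms of the likelihood ratio test nor any gating by it is stated, so neither can be relied on to close the gap.

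**Conclusion.** The point holds as a limitation of the follow-up, not of the overall trajectory comparison. The level tests give sound statements about level, but they cannot separate a T0 gap that persists from different recovery. They also cannot show between which subgroups or in which interval change differs. At a 0.28 m/s gap the contrast is plain: about 95% flagged at each visit when recovery is identical, and 5% flagged at T3 when one subgroup has caught up completely, against about 5% and 98% for a contrast of change. The sizes rest on the plan's SD and correlation and on an assumed 29/30 split, assumed gaps, equal correlations and no dropout. Different subgroup sizes or gaps would change the percentages but not the mismatch between the two hypotheses.

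**What to change.** 1. State that the likelihood ratio test is of the subgroup-by-time interaction.
2. Add between-subgroup contrasts of change from the same mixed model, either from T0 to each visit or between adjacent visits, Tukey-adjusted over subgroup pairs. Name these as the follow-up on which any statement about differing recovery rests.
3. Keep the comparisons at single visits, labelled as comparisons of level only. They need not lose their tests.

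Time is already modelled as discrete, so the contrasts are linear combinations of coefficients from the fitted model and need no new data or model. The cost is a sentence or two in the analysis text and a few more contrasts to report and adjust for. Power for modest differences in change stays limited: about 52% for a 0.14 m/s gap that closes fully.

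### The exploratory growth-mixture search leaves out the one-class model, so it cannot report an absence of subgroups, and its joint AIC/BIC rule gives no decision when the two criteria disagree

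*Protocol article*

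**What the plan says.** The Statistical analysis section of the protocol article introduces the step with its status: "As an exploratory analysis, growth mixture models (GMMs) will be used to identify relevant subgroups with different trajectories". It then fixes the candidate set, "We will fit GMMs with two to five classes", and the selection rule, which is "based on the lowest value of the Akaike Information Criterion (AIC) and lowest value of the Bayesian Information Criterion (BIC"). Neither criterion has priority. Once classes have been chosen, "multinomial logistic regression models will be used to identify predictors of group-membership". The section has no branch for a result without subgroups.

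The same section plans a separate one-population analysis: "Linear mixed effects models will be used to model the trajectories of mobility measures for the total sample and for predefined subgroups". Nothing in the text compares that model with the mixture models by AIC or BIC. The paragraph on mixed models also allows mobility measures to be transformed, for example to a log scale, if the fit is inadequate.

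The second objective is to find subgroups whose mobility trajectories differ and to describe the patients in each. The mixture models are the only planned method that searches for subgroups not defined beforehand.

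**The concern.** A search over two to five classes can say how many subgroups fit best, given that there are at least two. It cannot say whether there are any. If patients differ only by ordinary between-person variation around one average course, the procedure still returns two or more classes, and the regression step still gives them a set of predictors.

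The second weakness is the word that joins the two criteria. Requiring the lowest AIC and the lowest BIC picks a model only when both point to the same one. If they differ, the text leaves the choice to be made after the results are seen.

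What is at stake is how the answer to the second objective can be read, because a report of distinct recovery patterns could come from the candidate set alone.

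**Working it through.** The plan states no figure for this rule, so there is none to reproduce. The check has three parts.

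**1. What the rule can return.** The candidates are K = 2, 3, 4, 5. Whatever the data, the selected K is at least 2. This follows from the text and needs no simulation.

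**2. When the criteria can disagree.** The planned minimum sample is 59 ("Thus, we decided to at least recruit 59 subjects").

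- AIC penalty per parameter: 2.
- BIC penalty per parameter: ln(59) = 4.08, with n counted as patients. Counting visits instead, n = 59 × 4 = 236 and ln(236) = 5.46.
- Assumed model form, which the article does not state: class-specific intercept and slope, class proportions, and a shared compound-symmetric covariance. The parameter count is 2K + (K − 1) + 2 = 3K + 1, so each added class costs 3 parameters.
- AIC prefers the larger of two adjacent models when twice the log-likelihood gain exceeds 3 × 2 = 6.
- BIC prefers it when that quantity exceeds 3 × 4.08 = 12.2.
- Between 6 and 12.2 the two criteria rank the pair differently. The exact limits change with the model form, but a gap exists whenever ln(n) exceeds 2.

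**3. What including one class would change.** Two simulations drew data from one homogeneous normal population. From the Sample size calculation section they took the SD ("the standard deviation of the walking speed was assumed to be 0.3 m/s at each time point") and the correlation of 0.6 ("We think that a correlation of at least 0.6 is plausible for these data"). Both used four visits and the model form above. Simulation A had 180 data sets and 5 random starts. Simulation B had 100 data sets, 8 starts, the plan's step of 0.14 m/s per visit and an assumed starting speed of 0.7 m/s. B was repeated at n = 50, because 59 × 0.95³ = 50.6 patients would complete all visits under the stated dropout.

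| One true class, normal data | A, n = 59 | B, n = 59 | B, n = 50 |
|---|---|---|---|
| At least two classes returned, K = 2–5 | 100% (by construction) | 100% (by construction) | 100% (by construction) |
| BIC chooses one class, K = 1–5 | 99% | 100% | 97% |
| AIC chooses one class, K = 1–5 | 80% | 84% | 76% |
| AIC and BIC disagree, K = 2–5 | 9% | 21% | 20% |

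In this setting the model left out is the one both criteria usually prefer.

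Three further results from simulation B bear on the fix:

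- Adding K = 1 does not remove disagreement. It remained at 16% (n = 59) and 23% (n = 50), so a deciding criterion is needed as well.
- With two true classes (separation assumed, n = 59), AIC and BIC disagreed in 28% within K = 2–5. With K = 1–5, BIC chose two classes in 93% and one in 7%. AIC chose two in 71%, one in 1%, and more than two in 16% + 8% + 4% = 28%.
- With one skewed population analysed without transformation (an assumed scenario), adding K = 1 helped little: BIC chose it in 13% and AIC in 0%. The scale on which the models are fitted therefore matters.

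**The case against.** The strongest defence is the label. The analysis is called exploratory, the sample size was set for a mixed model of walking speed, and no confirmatory test depends on the mixture models. This stands and limits the severity. It does not repair a search that has no negative outcome.

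It can also be said that the total-sample mixed model is close to a one-class model, and that comparing predefined subgroups by likelihood ratio test can give a null result. Both are true. But the total-sample model is not in the AIC/BIC comparison, and predefined subgroups do not address whether latent ones exist.

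A tie-break might be thought a detail for a full analysis plan that is not shown. That argument has some force for the tie-break. It has none for the class range, which the article itself fixes.

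Some stronger readings are tempting and are not supported:

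- A reader might infer that any subgroups found would carry no evidence. Only the return of at least two classes is guaranteed. Class sizes, trajectories and fit would still be informative, and real classes could be found.
- A reader might take the disagreement rates as estimates for this study. The 9% and 21% for nominally the same scenario differ by about 2.6 standard errors (0.12 / √(0.09 × 0.91/180 + 0.21 × 0.79/100) = 0.12 / 0.046). They depend on modelling choices that the documents do not give.
- A reader might cite skewed data as proof of failure. The skewed population is assumed, and the plan's transformation clause goes some way to meeting it.
- A reader might object that no minimum class size is set. A condensed article may leave that to a fuller document, so it is not counted here.

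**Conclusion.** The point holds, at moderate severity. As written, the exploratory search cannot conclude that no distinct subgroups are supported, and the joint criterion has no outcome when AIC and BIC differ. Both conclusions follow from the text and do not depend on any simulation.

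The size depends on the truth. If patients form one homogeneous normal population with the plan's SD and correlation, BIC would have chosen the excluded model in 97% to 100% of data sets and AIC in 76% to 84%. These figures assume linear growth and a shared covariance, which the article does not specify. The disagreement rates show only that the gap can occur. The powered mixed-model analysis of walking speed is unaffected.

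**What to change.** In the Statistical analysis section:

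1. Fit one to five classes, so that the one-class model is a candidate.
2. Name one deciding criterion in advance, for example BIC, and report the AIC choice as a sensitivity result.
3. State that the transformation rule already planned for mobility measures is applied before the mixture models are fitted.
4. State that if one class is selected, the report says that no distinct subgroups are supported and the multinomial step is omitted.

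The cost is one extra model fit per measure and a few sentences. The exploratory analysis may end without subgroups. A stricter criterion such as BIC can also miss real classes, as in the 7% of simulated two-class data sets above, which is a reason to report AIC beside it.

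A cap of three classes, a floor of about 10% of patients per class and a bootstrap likelihood ratio test are optional. The documents do not require them, and the bootstrap test would add more computation than one fit.
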